## Abstract

**Background:**

Postoperative delirium (POD) is an acute mental disorder that often occurs in the elderly after surgery. It can delay functional recovery, extend hospital stay, and increase 1-year mortality and financial costs. Studies have shown that inflammation and cerebral desaturation are the potential pathogenesis of postoperative delirium. Prone-position surgery increases peak airway pressure and decreases lung compliance, exacerbating ventilator-induced inflammation response, as well as the decrease of the patient's cerebral oxygen saturation. Recent studies demonstrated that lung-protective ventilation strategy could reduce inflammatory response and improve cerebral oxygen saturation (rSO_2_) to prevent POD. In this trial, we aim to investigate the effect of the individualized PEEP on postoperative delirium in elderly patients during prone position.

**Methods:**

A prospective, randomized clinical trial will be performed in Hebei General Hospital. 106 patients undergoing elective surgery in prone position will be randomly divided into controlled group (group C) and individualized PEEP group (group I). Lung-protective ventilation with tidal volume of 6ml/kg predictive body weight (PBW) and positive end-expiratory pressure (PEEP) of 5 cm H_2_O will be applied to patients in group C. Patients in group I will receive the same tidal volume as described in group C plus individualized PEEP corresponding to the maximum dynamic compliance (Cdyn) in the titration method. Our primary endpoint is the prevalence of postoperative delirium based on the Confusion Assessment Method (CAM) until postoperative day 3. Secondary endpoints include the intraoperative rSO_2_, respiratory variables, arterial blood gases, lung ultrasound score (LUS), postoperative VAS score, and plasma concentrations of IL-6, IL-1β and neuron-specific enolase (NSE).

**Discussion:**

The results of the current protocol might provide evidence for individualized PEEP to prevent POD among older surgical patients in prone position.

**Trial registration:**

Chinese Clinical Trial Registry (ChiCTR2200056001). Registered 2022 January 30, http://www.chictr.org.cn/index.aspx.

## Background

Postoperative delirium, a serious postoperative neurological complication, characterized by acute and fluctuating changes in consciousness and attention, can increase morbidity and mortality in patients over 60 years of age [1]. Due to different types of surgery, POD in elderly patients has been reported to occur in 10%-60% [2].

Mechanical ventilation could induce proinflammatory response and ventilator-induced lung injury (VILI), which may increase the incidence of POD [3, 4]. The prone position is commonly used during percutaneous nephrolithotripsy or spine surgery to provide a fine condition for the operation. However, this non-physiological position can cause increased peak airway pressure (P_peak_), decreased Cdyn, thus aggravating lung injury [5, 6]. In addition, perioperative cerebral desaturation may increase the risk of POD among different types of surgery [7, 8]. Significantly, cerebral desaturation commonly occurs in elderly surgical patients undergoing prone position [9]. Thus, patients undergoing prone position may be at high risk of POD owing to decreased rSO_2_ and VILI-induced inflammatory response. Recent research suggested that intraoperative lung-protective ventilation might help prevent POD by inhibiting inflammation and improving rSO_2 _[4].

Intraoperative lung-protective ventilation strategies, including low tidal volumes (V_T_), PEEP, and recruitment maneuvers (RM), have been proved to alleviate lung injury and prevent POD [4, 10]. Our previous studies have shown that individualized PEEP combined with pressure-controlled ventilation-volume guaranteed (PCV-VG) mode could mitigate lung damage, and lead to favorable oxygenation in patients undergoing thoracoscopic surgery and laparoscopic surgery [11, 12]. Recent studies demonstrated that the application of PEEP could induce significant increases in rSO_2_ [4, 13]. Whether individualized PEEP could prevent POD is not clear. Hence, we hypothesized that individualized PEEP can prevent POD by reducing inflammatory response and improving rSO_2_.

Based on the above studies, our aim is to explore the neuroprotective effect of individualized PEEP among elderly patients undergoing mechanical ventilation in prone position. This trial will replenish further clinical evidence of employing intraoperative individualized PEEP to prevent POD.

## Methods

This study has been approved by the Ethics Committee for Clinical Trial of Hebei General Hospital, China (no.2019–48) and has been registered in the Chinese Clinical Trial Registry (registration number ChiCTR2200056001).

### Trial design

This single-center, prospective, randomized controlled trial is designed to explore whether individualized PEEP application would prevent POD in elderly surgical patients in prone position. Figure 1 shows the Flow chart of the trial. This study will be performed at Hebei General Hospital according to the standard protocol items for randomized trials [14]. The investigators will collect data from the day before surgery to the time the patients are discharged from the hospital (Table 1).

**Table 1. Tab1:**
[figure not shown]
Standard Protocol Items: Recommendations for Interventional Trials (SPIRIT) Schedule for enrollment, interventions, and assessments. T0: after entering the operating room, T1: 5 minutes after starting mechanical ventilation in the supine position, T2: 60 minutes after turning over, and T3: 5 minutes after taking in the supine position, T4: after breathing air in PACU for 20 minute

**Fig. 1 Fig1:**
[figure not shown]
Flow chart of the trial

### Randomization and blinding

The trial is single-blind because the attending anesthesiologist will collect data and perform PEEP titration without being blinded to the group assignments. Based on a computer-generated randomization sequence performed by an independent investigator, the selected participants will be randomized into Group I and Group C. Envelopes with random numbers will be opened when patients enter the operating room. The allocation ratio is 1:1. Postoperative information collection and the following data analyses will be performed by another researcher who will not participate in this study and know about the grouping allocation.

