### Inclusion criteria

Patients who plan to undergo elective surgery in prone positions will be included according to the criteria below: (1) ASA physical status II and III; (2) ≥ 65 years old; (3) baseline mini-mental state examination (MMSE) [15] score > 23 points evaluated one day before surgery.

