### Discharge criteria

The discharge criteria are as follows: (1) baseline rSO2 < 60%; (2) the operation time > 4 h, (3) intraoperative blood loss > 800 ml; (4) interruption of study protocol.

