### Sample size calculation

G∗power (version 3.1.9.6) is used to calculate the sample size. A total of 16 (8 in the I group and 8 in the C group) patients were included in our preliminary experiments. The number of patients diagnosed with POD was 2 in the I group and 3 in the C group, respectively. On this basis, the calculated sample size that would provide 80% power to detect this difference at a two-sided significance level of 0.05 was 42 patients per group. Considering a dropout rate of 20%, 106 patients will be enrolled in this study.

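### The one stratum named for the Mantel-Haenszel comparison of delirium arises after randomisation and only in Group I, while surgery type, which the protocol itself ties to delirium risk, is not named as a stratum

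*Protocol article*

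**What the plan says.** **Case mix.** The Inclusion criteria section restricts by ASA status, age and MMSE score but not by procedure: "Patients who plan to undergo elective surgery in prone positions will be included according to the criteria below". The Background gives two procedures as examples: "The prone position is commonly used during percutaneous nephrolithotripsy or spine surgery to provide a fine condition for the operation".

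**Risk by surgery type.** The Background also states: "Due to different types of surgery, POD in elderly patients has been reported to occur in 10%-60" (per cent). The range refers to elderly surgical patients in general.

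**Allocation.** The Randomization and blinding section says: "Based on a computer-generated randomization sequence performed by an independent investigator, the selected participants will be randomized into Group I and Group C". It adds "The allocation ratio is 1:1" and envelopes opened on entry to the operating room. It mentions neither strata nor blocks.

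**Analysis.** The Statistical methods section plans a Mantel-Haenszel test of delirium risk. It names one stratifying factor, whether MAP falls below 55 mmHg during the PEEP titration, and then refers to further possible confounders without naming them. Under Interventions, only Group I is titrated. Group C stays at 5 cm H2O throughout.

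**Effect sought.** The Sample size calculation section rests on a pilot with 8 patients per group: "The number of patients diagnosed with POD was 2 in the I group and 3 in the C group, respectively".

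**The concern.** The protocol identifies surgery type as a driver of its primary outcome, admits a mix of procedures, and states no control for surgery type in either allocation or analysis. The analysis section does commit to a stratified test, but the factor it fixes cannot do the work of a baseline stratum. It is observed after allocation, and it is defined by a procedure that only one arm undergoes.

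At stake is precision. If prone procedures differ in delirium risk, an unadjusted comparison carries avoidable variance, and in a single trial of this size the observed difference can move by a few points for reasons unrelated to PEEP. A named baseline stratum would remove that component. The unnamed confounders leave the choice open, possibly until after the data are seen.

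**Working it through.** **Inputs from the protocol article**
- Pilot delirium: 3/8 = 37.5% in Group C and 2/8 = 25% in Group I, a difference of 12.5 points (Sample size calculation).
- 42 per group before dropout and 106 enrolled, that is 53 per group (same section).
- Delirium 10% to 60% by surgery type (Background).

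**Assumed, because not given**
- Two surgery types. The higher-risk type makes up 50% of patients, with 20% and 30% also tried.
- A risk contrast between types of 50 points (the whole quoted range) or 20 points.

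**1. The plan's own figures.** The dropout step reproduces: 42/(1 − 0.20) = 52.5, rounded up to 53 per arm, 106 in all. The 42 does not follow from the pilot rates. The usual two-sided formula gives

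n = [1.960·√(2 × 0.3125 × 0.6875) + 0.842·√(0.375 × 0.625 + 0.25 × 0.75)]² / 0.125² ≈ 215 per arm.

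That is a separate and larger problem. It is noted here because it explains the low power in step 5.

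**2. What the MAP stratum contributes.** Take the stratum with MAP below 55 mmHg during titration. All T patients in it belong to Group I, and x of them have delirium. With n₁ = T and n₀ = 0, the Mantel-Haenszel expectation is T·x/T = x, and the variance is T·0·x(T − x)/[T²(T − 1)] = 0. The stratum adds nothing and those patients drop out of the comparison. What remains is Group I patients without that hypotension against all of Group C, a contrast selected on a post-randomisation event.

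**3. Size of a chance imbalance in surgery type.** At 53 per arm and a 50:50 mix, the SD of the between-arm difference in the share of one type is √(2 × 0.25/53) = 9.7 points. Multiplying by the risk contrast gives the SD of the shift in the delirium difference:
- 50-point contrast: 9.7 × 0.50 = 4.9 points, or 39% of 12.5.
- 20-point contrast: 9.7 × 0.20 = 1.9 points.

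Simulated allocations (400,000 per setting, under both independent assignment and equal arms) give the chance of a shift of at least half the pilot difference (6.25 points, either direction):

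| Per arm | Higher-risk share | Contrast | Shift ≥ 6.25 | Shift ≥ 12.5 |
|---|---|---|---|---|
| 53 | 50% | 50 points | 21% to 24% | under 1% |
| 53 | 20% or 30% | 50 points | 10% to 16% | under 1% |
| 42 | 20% to 50% | 50 points | 10% to 27% | 0.4% to 2.2% |
| 42 or 53 | 20% to 50% | 20 points | under 0.5% | none seen |

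**4. Why this is variance and not bias.** Under no treatment effect, with risks of 10% and 60% in equal shares, the overall risk is 35%. The variance of the crude difference is 2 × 0.35 × 0.65/53 = 0.00858. It splits into a within-type part, 2 × (0.09 + 0.24)/2/53 = 0.00623, and an imbalance part, 2 × 0.25 × 0.50²/53 = 0.00236. The imbalance part is 27% of the total, and the crude test's standard error already includes it. Stratifying lowers the SD from √0.00858 = 9.3 points to √0.00623 = 7.9. With risks of 10% and 30%, the same split gives 0.00038 out of 0.00604, or 6%.

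**5. Effect of stratifying the test by surgery type.** Forty thousand simulated trials per setting, 53 per arm, 50:50 mix, control risks 10% and 60%:
- Type I error: 5.4% for the unstratified chi-square, 5.0% for Mantel-Haenszel.
- Power at the pilot odds ratio, (0.25/0.75)/(0.375/0.625) = 0.56: 18.7% against 22.4%, a gain of 3.7 points.

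Across 42 or 53 per arm and a 30% or 50% share, the gain runs from 2.1 to 3.7 points. Under a 20-point contrast there is no material gain.

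**The case against.** Several stronger readings are tempting, and the documents do not support them.

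- **That randomisation is simple.** A reader might infer this from the silence on strata and blocks. The article says only that the sequence is computer-generated, and an article may leave list details to the full protocol. What can be said is that no stratification by surgery type is stated.
- **That prone procedures differ by 50 points.** The 10% to 60% range covers elderly surgery in general. No rates are given for spine surgery or percutaneous nephrolithotripsy. Eligibility limits, and the removal of operations over 4 h or with blood loss over 800 ml, probably narrow the spread, although those removals come after the envelope is opened and so cannot secure balance. At 20 points the effect is negligible.
- **That imbalance could create or cancel the effect sought.** A shift of the whole 12.5 points occurs in under 1% of trials at 53 per arm even in the extreme case, and type I error stays near 5%.
- **That the biomarkers and pain scores are distorted too.** The documents give no figures for these by procedure.

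It can also be argued that naming the confounders belongs in the SAP, which is not shown, and that surgery type could be among them. That is fair for the unnamed factors. It does not excuse the named one: the protocol has already fixed a stratum, and that stratum is not a baseline factor.

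**Conclusion.** The point holds as one about the analysis stratum. The protocol ties delirium risk to surgery type, pools all elective prone surgery, and commits its stratified comparison to a factor that arises after allocation and in one arm only. That factor cannot adjust for any baseline difference, surgery type included.

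The consequence is lost precision and nothing more. The 4.9-point SD and the 21% to 24% chance of a half-effect shift rest on 53 per arm, a 50:50 mix of two types and the full 50-point contrast. With a 20-point contrast they fall to 1.9 points and under 0.5%. Neither the mix nor the contrast is known from the documents. Stratifying does not rescue the power, which stays near 22% at the pilot odds ratio in the most favourable setting simulated.

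**What to change.** In the Mantel-Haenszel comparison of delirium, replace the MAP stratum with planned surgery type, for example spine versus percutaneous nephrolithotripsy or other. Record it at consent the day before surgery, so that it precedes the opening of the envelope, and apply it to all 106 patients. State it before the allocation is revealed to the analyst. Hypotension during titration can still be reported descriptively for Group I, since the Safety evaluation section already counts hypotension as an adverse event.

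Optionally, stratify the randomisation list by surgery type with permuted blocks of varying size for patients still to be enrolled. The 12 already recruited at submission would be placed in their strata afterwards.

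Cost: one sentence and an amendment for the analysis change, plus a new list and separate envelope sets for the optional one. A sparse surgery type would add little information and could leave a block incomplete. The power gain is about 3 to 4 points under the 50-point contrast with an even mix at 53 per arm, and about none under 20 points.

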### Interventions

Noninvasive blood pressure (NIBP), electrocardiogram, pulse oxygen saturation, bispectral index (BIS), body temperature, and rSO_2_ of patients in each group will be routinely monitored after entering the operating room. We will place two brain oxygen electrodes 4 cm from the forehead to the brow arch (one on the left and another on the right) to measure rSO_2_ by using near-infrared spectroscopy (NIRS). After placement of monitors, radial artery puncture and catheterization will be performed under local anesthesia, allowing intermittent blood gas analyses and continuous hemodynamic monitoring.

Patients will receive intravenous propofol (2 mg/kg), sufentanil (0.3 µg/kg), and cisatracurium (0.15 mg/kg) for anesthesia induction and tracheal intubation after preoxygenated (inspired oxygen fraction of 0.8) for three minutes. During surgery, sevoflurane inhalation and continuous intravenous remifentanil and propofol infusion will be employed to maintain BIS between 40 and 60. Intermittent administration of cis-atracurium will provide sufficient muscle relaxation. Vasoactive drugs will be used to maintain mean arterial pressure (MAP) and heart rate within ± 20% of the baseline. The core temperature will be maintained above 36.0 ℃ by using a forced air warming system. Subsequently, when patients can respond to verbal commands, they will undergo extubating procedures and be transferred to the postanesthesia care unit (PACU) until fully awake. Patients will routinely receive intravenous patient-controlled analgesia (PCIA) to control postoperative pain.

Mechanical ventilation will be maintained with V_T_ 6 ml/kg PBW, FIO_2_ of 50%, and I: E of 1:2 with PCV-VG mode. After the prone position is established, both groups will receive the recruitment maneuver by squeezing a reservoir bag up to 30–40 cm H_2_O for 15–20 s. The initial respiratory rate will be set to 12 breaths per minute and P_ET_CO_2_ is maintained in the range of 40 ± 5 mm Hg by adjusting the respiration rate.

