The patients in both groups will receive the PEEP of 5 cm H_2_O after endotracheal intubation, and this PEEP level will be maintained throughout the whole procedure in the group C. After the prone position is set up, patients in Group I will receive optimal individualized PEEP identified by an incremental PEEP titration protocol (Fig. 2). The PEEP titration method is as follows: each PEEP level (4, 6, 8, 10, 12, 14, 16 cm H_2_O) will be maintained for 60 s. Meanwhile, we will record the Cdyn at each PEEP level. We will select the optimal PEEP level based on the maximum Cdyn and maintain it throughout the whole study period. If circulatory instability occurs during PEEP titration, intravenous infusion of noradrenaline will be used to maintain MAP ≥ 55mmHg.

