### Outcome assessment

The primary endpoint of this trial will be the incidence of POD within 3 days after surgery. POD will be determined by an independent researcher who will not know the group assignment using CAM [17]. The investigator will participate in a training session including symptoms and diagnosis of delirium and will not know the group assignment. The researcher will assess POD once daily, between 6: 00 am to 8: 00 am. Four key delirium characteristics consist of CAM diagnostic criteria: (1) acute onset and disease fluctuations, (2) inattention, (3) changes in consciousness, and (4) disordered thinking. Delirium will be defined as the presence of (1) and (2), accompanied by (3) or (4) or both [7].

The secondary outcomes will include perioperative rSO_2_ measurement, arterial blood gases, respiratory variables, and plasma concentrations of interleukin (IL)-1β, IL-6, and NSE. The baseline rSO_2_ will be obtained within 2 minutes before anesthesia induction and averaged. Additionally, intraoperative rSO_2_ values will be continuously measured and recorded using a cerebral oximeter at the following timepoint: T_0_: after entering the operating room; T_1_: 5 minutes after starting mechanical ventilation in the supine position; T_2_: 60 minutes after turning over; and T_3_: 5 minutes after taking in the supine position. The serum concentrations of interleukin (IL)-1β, IL-6, and NSE will be determined by ELISA kits. We will collect the blood samples 15 minutes before anesthesia induction (T_0_) and postoperative day 1.

Arterial blood gases will be measured at T_1_ to T_4_ (after breathing air in PACU for 20 minutes). Respiratory variables including P_ET_CO_2_, PEEP, P_peak_, mean airway pressure (P_mean_), Cdyn, PaO_2_/FiO_2_, A-aDO_2_, V_D_/V_T,_ and Qs/Qt will be recorded at T_1_ to T_3_. Each patient will receive two ultrasound examinations at T_1_ and T_4_. And lung ultrasound scans will be performed by an experienced anesthetist who will not know the group allocations. As described previously [18, 19], each hemithorax will be alienated into 6 quadrants and each region will be assigned a score of 0 to 3 according to the different signs of B-line, subpleural consolidation and pleural line under ultrasound scan. The LUS will be calculated to quantitatively assess the aeration loss by adding all scores up.

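### The allocation envelope is opened at entry to the operating room, although the arms do not differ until after prone positioning, so the anesthesiologist knows the group earlier than the design requires

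*Protocol article*

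**What the plan says.** Under Randomization and blinding, the protocol article fixes when the group becomes known: "Envelopes with random numbers will be opened when patients enter the operating room". It calls the trial single-blind because "the attending anesthesiologist will collect data and perform PEEP titration without being blinded to the group assignments".

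Under Interventions, one regimen of monitoring, induction, maintenance and ventilation is described for all patients. PEEP also starts out the same: "The patients in both groups will receive the PEEP of 5 cm H_2_O after endotracheal intubation". The first step that belongs to one arm only is the titration: "After the prone position is set up, patients in Group I will receive optimal individualized PEEP identified by an incremental PEEP titration protocol". A step common to both arms is also placed after turning: "After the prone position is established, both groups will receive the recruitment maneuver by squeezing a reservoir bag".

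Table 1 defines the early time points: "T0: after entering the operating room, T1: 5 minutes after starting mechanical ventilation in the supine position". Outcome assessment adds: "The baseline rSO_2_ will be obtained within 2 minutes before anesthesia induction and averaged".

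**The concern.** In a trial where the person giving the intervention cannot be blinded throughout, the usual safeguard is to delay disclosure until the arms have to be treated differently. Here disclosure comes at the start of the operating room stay, well before that moment.

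Two things are at stake:

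- **Care.** Part of the shared care leaves room for judgment, such as the mix of anesthetics used to reach the BIS target and vasoactive drugs used to hold pressure and heart rate within a band. Someone who knows the group can, without intending to, handle these differently by arm before any PEEP difference exists.
- **Readings.** Baseline rSO2, T0 and T1 are the pre-treatment reference for the secondary outcomes. Their value rests partly on being taken by someone who could not know the allocation.

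**Working it through.** The protocol gives no figure on this point, so the check is one of sequence.

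**Order of events**

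| Step | Source in the protocol article | Differs by arm? | Group already disclosed? |
|---|---|---|---|
| Consent and MMSE, the day before surgery | Study participants and recruitment; Inclusion criteria | No | No |
| Entry to the operating room, envelope opened | Randomization and blinding | No | Disclosed here |
| T0 and baseline rSO2 | Table 1; Outcome assessment | No | Yes |
| Induction and intubation | Interventions | No | Yes |
| Supine ventilation with the common PEEP | Interventions | No | Yes |
| T1 rSO2, blood gas and respiratory variables | Table 1; Outcome assessment | No | Yes |
| Turning prone | Interventions | No | Yes |
| Recruitment maneuver, both groups | Interventions | No | Yes |
| PEEP titration, Group I | Interventions | **Yes** | Yes |

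The last two rows are listed in the order in which the text describes them. The text does not state which of the two is done first, and Fig. 2 is not shown. Every row from T0 to turning prone is common to both arms and follows disclosure, whichever order applies.

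**Measurements that fall in this interval**

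- rSO2 is recorded at T0, T1, T2 and T3. T0 and T1 fall inside: 2 of 4.
- Respiratory variables are recorded at T1, T2 and T3. T1 falls inside: 1 of 3.
- Arterial blood gases are taken at T1, T2, T3 and T4. T1 falls inside: 1 of 4.
- Lung ultrasound is done at T1 and T4 by an operator who is kept unaware of the group, so the T1 scan is not exposed.

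**Does anything in this interval need the group to be known?** Nothing in Interventions makes induction, ventilator settings or PEEP before turning depend on the arm. The earliest step that needs the allocation is the titration.

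**Who knows?** The text does not say who opens the envelope. It does say that the attending anesthesiologist is unblinded and collects data. That this person knows the group once the envelope is open is the natural reading, though not an explicit statement.

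**The case against.** The strongest case on the other side is that later opening would gain little.

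- The anesthesiologist must know the group from titration onward. Most of the anesthetic, vasoactive and P_ETCO2 management comes after that, as do T2 and T3. This stands: the change shortens the unblinded period but does not end it.
- The primary endpoint is rated with the CAM by a trained assessor unaware of the group, and the early readings are instrument values. This also stands, and it limits the likely effect on the delirium result. It does not cover differences in care given before the rating.
- A condensed article may leave out a reason for the early opening. This is fair: no reason is documented, which does not show that none exists.
- Twelve participants had been recruited at submission, and changes go to the ethics committee. This is a real cost, but a small one.

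A reader might infer more than the document supports, in three ways:

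- **That the recruitment maneuver is certainly performed before the arms differ.** Both it and the titration are placed after turning, with no stated order.
- **That the latitude of the maneuver measures the bias.** The text has "both groups will receive the recruitment maneuver by squeezing a reservoir bag up to 30–40 cm H_2_O for 15–20 s", and the product of pressure and time runs from 30 × 15 = 450 to 40 × 20 = 800 cm H2O·s, a ratio of 800/450 = 1.78. This is a tolerance allowed equally in both arms. It is neither an observed nor an expected difference between them.
- **That every measurement before the arms separate is unblinded.** The T1 lung ultrasound is not.

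**Conclusion.** The point holds as an avoidable weakness of design. The protocol fixes disclosure at entry to the operating room, while its own sequence needs it only after the prone position is set up. Baseline rSO2, T0, induction, supine ventilation with the common PEEP, and the T1 rSO2, blood gas and respiratory readings all take place with the group known to the person who treats the patient and records the data.

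The size of any bias cannot be derived from the document. A modest effect is the reasonable expectation, given the blinded CAM rater and the many shared settings that are fixed. The document gives no ground for saying that the delirium comparison is biased, or that enrolment was steered, since consent is taken the day before the envelope is opened.

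The conclusion rests on one assumption: that the anesthesiologist learns the group when the envelope is opened. It does not depend on the order of maneuver and titration. That order matters only for whether the maneuver, too, could be given before disclosure.

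**What to change.** Amend Randomization and blinding so that the sealed envelope is opened only after the prone position is established and immediately before the first group-specific step. State that baseline rSO2, T0 and T1 values are recorded before it is opened, and name who opens it.

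In Interventions, the two statements that place the recruitment maneuver and the titration after turning should be reconciled so that their order is explicit. Which order applies is for the sponsor to settle. If the maneuver comes first, the envelope should be opened after it, so that it too is given without knowledge of the group.

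Cost: a short amendment with ethics review, and no added staff, procedures or patients. The anesthesiologist must be ready to titrate in every patient. Patients already enrolled were allocated under the present timing. At the reported status that is 12 of 106, leaving 106 − 12 = 94 who could follow the new one. The report should state when the change took effect.

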### Safety evaluation

The researchers will monitor all adverse events (AEs) associated with the PEEP titration procedure. AEs are defined as hypotension, significant cardiac arrhythmias, pneumothorax, significant disability or incapacity, and even death. The researchers will visit all patients in the trial daily until they are discharged from the hospital and record the occurrence of all AEs in detail. Once AEs occur, the trial will be suspended and an investigation will begin.

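### The data analyst's implied blind does not hold: PEEP recorded from T2 onward, and a positive titration-MAP stratum, identify the arm even under coded labels

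*Protocol article*

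**What the plan says.** The protocol article makes the trial single-blind because "the attending anesthesiologist will collect data and perform PEEP titration without being blinded to the group assignments". Other work goes to someone else. Randomization and blinding states: "Postoperative information collection and the following data analyses will be performed by another researcher who will not participate in this study". The rest of that sentence turns to this person's knowledge of the groups. Grammatically its negation is loose, but the evident intent is that this person does not know the allocation. The same sentence covers postoperative data collection and the analysis.

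Interventions starts both groups at a PEEP of 5 cm H2O after intubation and adds for the control arm that "this PEEP level will be maintained throughout the whole procedure in the group C". Titration is described for Group I only, after the patient is prone: "each PEEP level (4, 6, 8, 10, 12, 14, 16 cm H_2_O) will be maintained for 60 s". Then: "We will select the optimal PEEP level based on the maximum Cdyn and maintain it throughout the whole study period".

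Outcome assessment lists PEEP, with P_peak, P_mean, Cdyn and others, among the respiratory variables that "will be recorded at T_1_ to T_3". It also says that delirium is scored with the CAM by an independent researcher who is unaware of the group.

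Statistical methods plans a Mantel–Haenszel comparison of delirium risk. It is stratified by whether MAP fell below 55 mmHg during PEEP titration and by further possible confounders that are not named.

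**The concern.** A blinded analysis is useful only if the analyst cannot tell which code is which arm while choices remain. Here the file to be analysed contains the intervention setting itself, and one planned stratifier of the primary comparison is an event during a procedure that only one arm undergoes.

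Choices also remain. The unnamed confounders in the Mantel–Haenszel analysis leave the adjustment set for delirium to be decided. An analyst who can see the arms could settle that set knowing which way each choice moves the result. The trial could then report a blinded analysis that its own dataset contradicts. At stake is the credibility of the primary comparison at the analysis stage, not the validity of the delirium scores.

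**Working it through.** The protocol gives no figure to reproduce for this point. The check is a comparison of the PEEP values possible in each arm at each time point, followed by the same question for the stratifier.

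**Inputs**
- Group C level: {5} cm H2O, fixed (Interventions).
- Group I levels after titration: {4, 6, 8, 10, 12, 14, 16} cm H2O (Interventions).
- Recording times for PEEP: T1 (supine, 5 minutes after ventilation starts), T2 (60 minutes after turning prone), T3 (5 minutes after return to supine) (Outcome assessment).

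**PEEP by time point**

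| Time | Group C | Group I | Arms separated? |
|---|---|---|---|
| T1 | 5 | 5 (titration has not started) | No |
| T2 | 5 | 4, 6, 8, 10, 12, 14 or 16 | Yes, completely |
| T3 | 5 | same, if the titrated level is still held | Yes, on that condition |

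The intersection {5} ∩ {4, 6, 8, 10, 12, 14, 16} is empty. At T2 a value of 5 means Group C and any value on the titration grid means Group I.

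**What this does to coded labels.** With 1:1 allocation and 106 patients, 106 / 2 = 53 are expected per arm. Without other information, a guess at which code is Group I is right half the time. With the T2 column, one Group I patient treated per protocol shows which code is which, and so decodes the whole file.

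**Sensitivity to recording.** This assumes that the set PEEP is what is recorded. The distance from 5 to the nearest grid values is |5 − 4| = |6 − 5| = 1 cm H2O. If a measured value were recorded and could be off by that much, patients titrated to 4 or 6 could be confused with controls. The next level is 8 − 5 = 3 cm H2O away, so any patient at 8 or above would still be recognisable, and one is enough to break the code.

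**The stratifier.** Titration is described only for Group I, so MAP below 55 mmHg during titration can be positive only there. A negative value does not reveal the arm. With two coded groups, a single positive patient does reveal which code is Group I, within the delirium comparison itself and without the PEEP column. If no patient has the event, this route gives nothing.

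**The case against.** The strongest objection is that the delirium comparison does not need PEEP. Delirium is binary and is compared by chi-squared, Fisher or Mantel–Haenszel test; PEEP enters only the secondary respiratory analyses. Any trial that records its own intervention setting has this feature, and staged release of data is commonly left to an analysis plan or data-management plan, which is not shown here. This stands in part. It limits the consequence, and it means that the absence of a release procedure is not in itself a fault. It does not remove the conflict between an analyst presented as blind and a single analyst role given data that show the arms. Nor does it reach the titration stratifier, which is an input to the delirium comparison.

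A reader might go further and infer that the CAM assessor is unblinded too, because one sentence gives postoperative collection and analysis to the same researcher and because Safety evaluation says "The researchers will visit all patients in the trial daily until they are discharged from the hospital" in the context of adverse events of titration. The documents do not support this:
- Outcome assessment says twice that the person scoring delirium does not know the group.
- Nothing gives that person the ventilation record.
- Analysis follows collection, so a PEEP column seen at analysis cannot change scores already recorded.
- The safety visits cover all patients. The listed events (hypotension, arrhythmia, pneumothorax, disability, death) can occur in either arm, and recording them does not require knowing who was titrated.
- The visiting researchers are not identified as the CAM assessor.

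**Conclusion.** The point holds for the analyst and only for the analyst. From T2, recorded PEEP identifies the arm of every patient treated per protocol, and a positive titration-MAP stratum identifies Group I. Coding the groups therefore does not give the blinded analysis that the protocol implies.

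This rests on four assumptions: the loosely worded sentence means that the analyst does not know the allocation; set PEEP is what is recorded; Group I keeps a level from the titration grid at T2; and titration takes place in Group I only, as described. Separation at T3 further requires that the titrated level is still held then.

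No bias in the delirium estimate can be calculated from the documents. The exposure is the freedom left to the analyst, chiefly the unnamed confounders. It would be small if a full analysis plan already fixes them. Misclassification of delirium should not be charged to this point, because the assessor's blind is stated and nothing in the documents contradicts it. The protocol should be amended, but this is not a flaw that invalidates the primary endpoint.

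**What to change.** Amend Randomization and blinding and Statistical methods as follows.

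1. Name the primary delirium comparison and its stratification factors in advance, and restrict those factors to baseline variables. MAP during titration arises after allocation and in one arm only, so it does not belong in the blinded comparison.
2. Run and lock that comparison on coded groups, using a file without PEEP, P_peak, P_mean, Cdyn or any titration variable.
3. Release those variables only after the lock. Run the secondary ventilatory analyses, and any analysis stratified by MAP during titration, at that stage, and describe them as unblinded.

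Optionally, add one sentence to Outcome assessment and Safety evaluation stating that the CAM assessor has no access to the anesthesia record or to the form for titration adverse events. This is a clarification, not the repair of a demonstrated breach.

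The cost is protocol wording and a two-step data release, with no extra patients or measurements. The small downside is that the secondary ventilatory analyses start after the delirium lock. Trial status reports 12 participants recruited at submission, so at that stage the change could still precede any outcome analysis.
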